## Methods

### Study design and procedures

This study is a prospective longitudinal observational cohort study, taking place over a period of 2 months, with an intensive-longitudinal ecological momentary assessment (EMA) phase (Fig. 2). Participants provide self-report questionnaire data at baseline (Time 0, T0), with subsequent follow-up questionnaires (Time 1–3, long-longitudinal design; LL) collected electronically via an online survey platform (Unipark, Tivian XI GmbH, Cologne, Germany) from a study tablet or computer on-site (T0) or on a personal device at home (e.g., computer, tablet, smartphone; Time 1–3). The study will involve a 1.5 h baseline session at MSB Medical School Berlin or Charité Universitätsmedizin Berlin or participants’ workplace, during which demographics, PA and sedentary behavior, physical and mental health, as well as theory-driven psychological variables will be assessed. During the baseline session, participants will also undergo objective measurements of their back posture and mobility. Participants will then receive training in the time-sampling protocol, the handling of their Android study phone (Nokia 6.3) with the movisensXS app (movisens GmbH) and accelerometer (Move4, movisens GmbH). Starting at T0, participants will wear an accelerometer and will be asked to complete three daily questionnaires on their study smartphone for the following 14 days (intensive-longitudinal design; IL; Fig. 2). Participants will receive three alarm-triggered daily life surveys via the movisensXS app at 8 am (“morning questionnaire”), 3 pm (“after work questionnaire”), and 9 pm (“evening questionnaire”). Participants can delay responding until 3 h after the time prompt, and reminders are sent every 20 min during this window. After this time, the questionnaires will no longer be available to prevent backfilling. Daily life assessments take 2 to 6 min each to complete, resulting in a total of 1.5–4.5 h to complete the diaries over the entire IL phase. Accelerometers will be worn on a belt clip placed at the right hip (i.e., the right anterior iliac crest) and do not require any attention from participants. Participants are instructed to wear the accelerometer during waking hours for 2 weeks and to recharge the battery at least every 5 days. Throughout the study, participants are encouraged to carry out their usual daily activities. The device has no monitor and does not provide activity feedback. Within 2 weeks of the end of the intensive longitudinal phase (1–15 days), participants return their materials (i.e., study phone and accelerometer) and complete a 30-minute exit session to receive feedback on their back posture and mobility. Each participant will be compensated with a minimum of €40 for this study.

**Fig. 2 Fig2:**
[figure not shown]
Study design

A subgroup of interested participants will participate in an observational *N*-of-1 time-series approach [25] over 2.5 months with prospective IL assessments only. Baseline measurements are the same as in the main study including a self-report questionnaire and an objective back posture and mobility measurement, followed by 67 more days of EMA assessments. *N*-of-1 participants will not receive follow-up questionnaires. Within 2 weeks of the end of the IL phase (day 1–68), participants will return their materials (i.e., study phone and accelerometer) and complete a 60-minute exit session to receive feedback on their back and to take part in a data-prompted, qualitative interview [26, 27]. The university’s ethics committee at MSB Medical School Berlin granted approval on 29/03/2021 (approval number MSB-2021/62) for the study, including data management and data protection procedures. Written informed consent will be obtained from each participant prior to enrolment. The pre-registration in the publicly available German Clinical Trials Register (DRKS-ID: DRKS00025296) took place on 28/06/2021. The actual study start date was 22/07/2021 and recruitment continued until the end of the funding period (30/06/2024). All data will be stored on a secure server at the two institutions. Primary data, such as participant-reported outcomes, will be pseudonymized.

### Sample and recruitment

Working adults will be recruited in the greater Berlin area, Germany, through posters and leaflets, email newsletters, intranet postings, research fairs, social media postings and videos, as well as face-to-face presentations to recruit physiotherapists in their workplace. An optional registration website allows participants to leave their contact details. Participants responding to the advertisements will be emailed the participation information and invited for a brief introductory telephone call to explain the procedure, to review inclusion and exclusion criteria, and to schedule a baseline appointment. After receiving verbal and written information, participants provide written informed consent to participate in the study at the start of the baseline session. Participants will have the option to participate in the *N*-of-1 design instead of the main study. Due to the different data protection components (e.g., audio-recording for semi-structured interviews) between the main sample and the *N*-of-1 sub-sample, participants will receive separate information material and written consent forms.

### In- and exclusion criteria

Individuals must be aged between 18 and 64 and working in one of two possible working conditions, either in a predominantly sedentary job (e.g., “office work”) or as physiotherapist (predominantly manual job) for at least 20 h per week, to take part in the study. Individuals should also be able to hear a smartphone-based alarm and be able to read and understand normal German text on a 10-inch tablet and 6-inch smartphone.

Exclusion criteria are: acute and chronic pain [28, 29] (i.e., “pain that persists or recurs for longer than 3 months”), an acute infection, pregnancy, professional, competitive, and top athletes, radicular symptoms, sensory deficits, or neurological diseases, fractures of the spine, diagnosed osteoporosis, strong deformations, or misalignment of the spine (e.g., highly pronounced, structural scoliosis or severe M. Bechterew), recent pelvis operation (3 months post), past spine operations, tumor diseases and bone metastases, inflammation of the spine, spinal stiffening surgery in the past, strong drug therapy (opioids / muscle relaxants / anti-epileptic drugs), an inability to perform the back measurements (max. flexion / extension, and max. lateral bending to the left and right side) as well as current participation in another study. To facilitate the interpretation of back posture and mobility measurements we further exclude persons with a BMI above 29.4 kg/m².

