**Job demands and resources**				
Did you work today? *1 (yes) − 2 (no); [If 1 (yes)]* From when until when did you work today? *From (time*, e.g.,* 9:00 am) ___ Until (time*, e.g.,* 4:00 pm) ___;* Have you taken at least one break of at least 15 min today? *1 (yes) − 2 (no)*; *[If 1 (yes)]* How long was your break? If you took more than one break, think of the longest. *From (time*, e.g.,* 12:00 pm) ___* *Until (time*, e.g.,* 1:00 pm) ___*	Working hours and breaks	-	-	x
Are you still working? *1 (yes) − 2 (no) – 0 (I did not work today)*; *[only for 1 (yes) and 2 (no)]* Are you working from home today? *1 (yes) − 2 (no)*	Work place	-	x	-
How often have you been under time pressure for professional reasons today? *1 (very seldom/never) – 5 (very often/always)*	Time pressure	-	x	-
Were you able to choose the way you did your work today? *1 (very seldom/never) – 5 (very often/always)*	Job control	-	x	-
This evening I didn’t think about my work at all. (Item 1)/ This evening I used the time to relax. (Item 2)/ This evening I did things that challenged me. (Item 3)/ This evening I felt I could decide for myself what to do. (Item 4) *1 (does not apply at all) − 5 (applies completely)*	Recovery experience	-	-	x

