##### Self-report EMA measures

Participants will be asked to complete self-report EMA measures at a pre-specified time each day. Measures taken at each data collection point in the morning will include *intention*,* self-efficacy* [43, 44], *planning* [48], and *affect* [58, 59]. Measures taken at each afternoon data collection occasion will include *social support* [63, 64], *time pressure*, and *job control*, adapted from [55]. Measures taken at each data collection point in the evening will include LTPA, *plan enactment*, adapted from [65], *habit strength* [50], *low back health*,* LBP intensity* and *disability* [39], *working hours*, *breaks*, and *recovery experience* [66] (Table 2). Each evening, participants are asked how typical their day was and whether anything unusual happened that could have affected their LTPA or accelerometer. In terms of LTPA, participants report whether they did any activity, and if so, what activity they did, when they did it and how long it lasted. This information is used to validate the accelerometer data and to determine the type of LTPA for descriptive purposes (Table 2). At the first follow-up of the LL phase, we also assess reactivity to the IL phase assessment (Table 1).

To obtain an objective measure of LTPA, we use the self-reported work time as a marker for the accelerometry data. By combining these two sources of data, we will be able to distinguish between accelerometer data during work and during non-work time (i.e., leisure-time). The same procedure will be used to obtain a measure for sedentary time during work and leisure-time.

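### Daily time pressure and job control are rated only at a fixed 3 pm prompt with no answer for a shift not yet begun, so on late-shift days they can describe work not yet done

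*Protocol article*

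**What the plan says.** All references are to the protocol article.

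- *In- and exclusion criteria*: participants need a predominantly sedentary job or work as a physiotherapist ("predominantly manual job) for at least 20 h per week, to take part in the study"). No shift pattern or start time is required or excluded.
- *Study design and procedures*: the second daily prompt is fixed at "3 pm (“after work questionnaire". "Participants can delay responding until 3 h after the time prompt", and "After this time, the questionnaires will no longer be available to prevent backfilling".
- *Self-report EMA measures*: time pressure and job control belong to the afternoon set ("Measures taken at each afternoon data collection occasion will include").
- Table 2, *Job demands and resources*: the two items are "How often have you been under time pressure for professional reasons today" and "Were you able to choose the way you did your work today", each on a 1 to 5 frequency scale and marked for the afternoon only. The afternoon status item, "Are you still working", can be answered yes, no, or that the person has not worked that day. The evening set asks whether the person worked and from when until when.
- *Within-person research questions*: higher job demands and lower job resources than usual are expected to go with less LTPA, on the same day and from one day to the next.

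**The concern.** Both items ask about the whole day, but the clock decides how much of the working day the answer covers. Someone who has finished work rates a complete shift. Someone part-way through rates a fraction. Someone yet to start rates nothing real, and none of the three status answers describes that situation well. Time pressure is the only daily job-demand item, so no other daily measure can stand in for it.

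At stake is the within-person hypothesis on job demands and resources. Invalid ratings dilute a true association. Shift timing also determines when leisure falls, because LTPA is MVPA outside working hours. It can therefore move both the recorded predictor and the outcome, and an association of either sign could arise without a true effect.

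**Working it through.** The article gives no figure for late shifts or for how much of a shift a rating covers, so it has no figure of its own to reproduce here.

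**1. Response window.** 15:00 + 3 h = 18:00.

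**2. Share of the shift worked at response** = hours worked by then / shift length, ignoring breaks. The first two rows use the article's own example times; the others are assumed.

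| Work time | Answer at 15:00 | Answer at 18:00 |
|---|---|---|
| 9:00–16:00 (Table 2 example) | 6/7 = 86% | 100% |
| 9:30–16:30 (*Objective EMA measures* example) | 5.5/7 = 79% | 100% |
| 7:00–15:00 | 8/8 = 100% | 100% |
| 14:00–20:00 | 1/6 = 17% | 4/6 = 67% |
| 16:00–20:00 | 0% | 2/4 = 50% |
| Start at 18:00 or later | 0% | 0% |

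The day-shift examples are nearly covered at the prompt and fully covered if the participant waits. The 14:00–20:00 shift cannot be rated in full at any point in the window. The 16:00 starter has nothing to rate at the prompt but can answer after starting. A start at 18:00 or later never has a fitting answer.

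**3. Dilution.** Suppose a share p of rated days carries a rating unrelated to that day's true demand, with unchanged mean and variance. Then observed r = (1 − p) × true r. With an assumed true r of -0.15:

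| p (assumed) | Days of 14 | Observed r | 150/(1 − p)², rounded up |
|---|---|---|---|
| 2% | 0.28 | -0.147 | 157 |
| 5% | 0.7 | -0.1425 | 167 |
| 10% | 1.4 | -0.135 | 186 |
| 20% | 2.8 | -0.12 | 235 |

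The last column scales the minimum of 150 persons that *Power analysis* gives for a small day-level correlation, taking the number needed as proportional to 1/r². For comparison, 252 recruited less 20% leaves 252 × 0.8 = 201.6. This is illustrative only: the 150 comes from published simulation heuristics, and the article names intention, not time pressure, as the example predictor.

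**4. Spurious association.** Assume no true effect, a rating fixed 1 SD low on late days, LTPA shifted by b SD on those days, and 1,500 independent workday observations. Then |r| = p(1 − p)b / √{[(1 − p) + p(1 − p)] × [1 + p(1 − p)b²]}. Rejection at the two-sided 5% level follows from z = |r|√1500.

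| p | b | \|r\| | z | Rejection |
|---|---|---|---|---|
| 2% | 0.3 | 0.006 | 0.23 | 6% |
| 5% | 0.3 | 0.014 | 0.55 | 9% |
| 10% | 0.3 | 0.027 | 1.05 | 18% |
| 20% | 0.3 | 0.049 | 1.88 | 47% |
| 20% | 0.1 | 0.016 | 0.63 | 10% |

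The result runs from near nominal to almost one half, driven entirely by inputs that the article does not supply.

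**The case against.** Much of the defence stands.

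- The eligibility sentence is not an error. It only shows that late shifts are not excluded; the weakness lies in the prompt time and the answer options.
- A late starter is not forced to report a day off. The plain no is also available, and with reminders every 20 minutes until 6 pm some will answer after starting.
- A reader might infer that late-shift days are lost or that LTPA is misclassified. They are not. The evening item records work times; these are checked for plausibility, corrected, and used to split the accelerometer signal. The questionnaire-based LTPA outcome does not use the 3 pm answer either.
- The afternoon-only restriction applies to the daily items. Job demands and resources are also measured at baseline and at 2, 4 and 8 weeks, and recovery experience is asked each evening. The follow-up questionnaires cannot test day-level hypotheses, however.
- A reader might infer a bias between the two work groups. The article does not say that either group works late. A stable difference drops out of a test on deviations from a person's usual level; only timing that varies within a person matters.
- The afternoon slot has merit: it usually places the predictor before evening activity. Moving the items to 9 pm would put them after the day's LTPA, in the questionnaire that reports it.
- Table 2 is condensed, so an unshown skip rule cannot be excluded. But the table does print filters elsewhere, including one before the work-from-home item, and shows none for these two ratings.

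None of this makes a rating given before the shift a valid measure of that day's demands. The evening record identifies such days but cannot recover the missing rating.

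**Conclusion.** The point holds in a limited form. As described, the afternoon questionnaire can collect time-pressure and job-control ratings for work not yet begun, and partial ratings on many other days, under a label that implies the working day is over. Only these two daily predictors, with the afternoon work-status and home-working entries, are affected, on a share of days that the article does not give.

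Under an assumed 2% to 20% of uninformative days, a within-person r of -0.15 would appear as about -0.147 to -0.12: negligible at the low end, a loss of one fifth at the high end. A stronger reading, that false positives approach one half, needs 20% late days, a full 1 SD drop in the rating, a 0.3 SD shift in LTPA and independent observations all at once. None of these comes from the article, and milder inputs give 6% to 18%. Spurious association is therefore a possibility to guard against, not a quantified result. It is still worth settling before analysis, because the invalid values feed a stated hypothesis and can be found from data the study already collects.

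**What to change.** Recruitment ran to 30/06/2024, so the remedy belongs in the analysis rules:

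1. Compare the evening start and end times with the afternoon response time, assuming the app stores that time.
2. Set time pressure and job control to missing when the rating was given before the shift began, or when a not-worked answer is contradicted by the evening entry.
3. Keep all other ratings in the main model and describe them as demands and control up to the time of response. Apply the same reading when they serve as previous-day predictors.
4. Add a sensitivity model restricted to, or adjusted for, the share of the shift completed at response.
5. Report the number of ratings removed, by work group, which would replace the assumed range above with a fact.

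Restricting the main model to completed shifts, or moving the items to the evening, is a debatable trade-off and is not needed.

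The cost is a few lines of data-cleaning code and the loss of some late-shift person-days from the job-demand models. Days without an evening entry cannot be classified; they stay in the main model and leave the sensitivity model.

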### Benefits and Harms

Due to the non-invasive nature of the back measurements, accelerometer measurements and questionnaires, we did not expect any harm beyond the time commitment of the participants. However, a few of the test positions of the back posture and mobility measurements (particularly leaning backwards and remaining in this position for a few seconds) might cause some sort of fatigue, effort or temporary discomfort for some of the participants. Participants will be compensated (see above), and those who study at the MSB Medical School Berlin in addition to their professional activities will receive additional course credits. Participants will be encouraged to report any adverse effects they may experience during their participation in the intervention over email, text message or by phone call to the study facilitator when they occur (Table 1).

**Table 1 Tab1:** Variables assessed during the long-longitudinal study period at different time points

Variable	Baseline		2 weeks	4 weeks	8 weeks
**Demographic information**: age, gender, job, children, family status, household members, education, vocational training, mother tongue, citizenship, income, smoking, pregnancy, diseases and disease-related impairment, medication intake, height and weight (to calculate BMI), occupational physical activity, intensity of patient contact (hands-on vs. hands-off; for physiotherapists only), primary place of work/home-office, COVID quarantine	x		-	-	-
**Behavioral outcomes**					
**Physical activity and sedentary behavior**: adapted International Physical Activity Questionnaire (IPAQ) long version	x		x	x	x
**Physical activity and sedentary behavior (objective)**: Move4 accelerometer	Continuous assessment			-	-
**Back posture and mobility**: Back Posture, Movement and Mobility (B-PMM) self-report questionnaire	x			-	-
**Back posture and mobility (objective)**: Medimouse IDAG	x			-	-
**Behavior-related outcomes with respect to the lower back**					
**Low back health**: single item adapted from the Veterans Rand 12-item Health Survey (VR-12)	x		x	x	x
**Back pain**: Chronic Pain Grade Questionnaire, disability due to back pain (Roland-Morris Disability Questionnaire)	x		x	x	x
**General mental and physical health**: Health-related Quality of Life (VR-12), depressive symptoms and anxiety (Patient Health Questionnaire-4, PHQ-4)	x		x	x	x
**Theory-driven psychological variables**					
**Activity-related cognitions**: outcome expectancies, risk perception, self-efficacy, intention, action and coping planning, action control, social support, habit strength (Self-report Behavioral Automaticity Index)	x		x	x	x
**Back-related beliefs**: fear of movement (Tampa Scale for Kinesiophobia), pain catastrophizing (Pain Catastrophizing Scale), fear avoidance beliefs for work-related physical activity (single item from Fear avoidance Beliefs Questionnaire)	x		-	-	-
**Job demands and resources**: job control (Instrument for Stress-Oriented Task Analysis), time pressure (Instrument for Stress-Oriented Task Analysis), recovery experience (Recovery Experience Questionnaire), organizational health climate towards physical activity (Organisational Health Behavior Climate Scale), work environment	x		x	x	x
**Affect**: Positive and Negative Affect Schedule	x		x	x	x
**General self-control**: Brief State Self-Control Capacity Scale	x		x	-	-
**Feedback from participants**					
Reactivity (to sensor, to smartphone-based EMA assessment), interference of study participation with daily life	-		x	-	-
Representativeness of intensive longitudinal phase for daily life	-		x	-	-
Feedback from participants with regard to study participation in general	-		-	-	x
Adverse effects	At any time				

### Measurements

#### Measures for the long-longitudinal phase

The study measures will be taken at four time points, at baseline (T0), and at three follow-up occasions at 2 (Time 1, T1), 4 (Time 2, T2) and 8 (Time 3, T3; Fig. 2; Table 1) weeks post-baseline. At baseline, participants are asked to self-report a number of key demographic variables, including age, gender, marital status, education, and work status. Time-varying demographics will be reassessed at follow-up including medication intake, quarantine, or working from home.

##### Primary outcome

Our primary outcome for the LL phase will be *LTPA*. We operationalize LTPA as minutes spent in moderate-to-vigorous physical activity (MVPA) outside of working hours. An adapted version of the long International Physical Activity Questionnaire (IPAQ) [30] is used to determine LTPA over the past 7 days. The original 27-item instrument assesses different intensities of activities in four domains (job, transport, domestic, and leisure) and time spent sitting. We adapted the instructions for domestic tasks to explicitly include caring for the family (e.g., looking after children, elderly people). For descriptive purposes, we also assess the type of domestic or leisure activity in each case (“What was the activity?“, translated from German). Validation of the German-language instrument by Wanner et al. [30] showed moderate relationships with objectively-assessed PA data, comparable to other self-report PA instruments. The validity of the IPAQ will also be empirically tested by determining the agreement with the accelerometry data from the present study. The IPAQ will be processed in line with the IPAQ protocol [31]. The primary outcome of LTPA for the LL design encompasses items assessed by the IPAQ from the domain of “leisure”. This covers only part of our definition of LTPA, with transport-related and domestic activities excluded. To aggregate activities of different intensities for LTPA, we will determine each activity’s MET-value (Metabolic Equivalent of Task; moderate activity = 4 MET, vigorous activity = 8 MET, walking = 3.3 MET, cycling = 6 MET), multiply it by the time spent in the activity and frequency per week, and sum all values to create MET-minutes per week from LTPA activities (LTPA MET-minutes/week).

